## Abstract

**Background:**

The contemporary management of type 2 diabetes (T2D) involves a multifaceted model of care integrating intensive management of lipids, blood pressure, and glucose, along with lifestyle modifications. Despite these efforts, cardiovascular disease (CVD) remains a leading cause of morbidity and mortality among patients with T2D, largely due to suboptimal adherence to preventive strategies. The VOLTAIRE trial aims to assess the impact of providing personalized cardiovascular risk information derived from computed tomography coronary angiography (CTCA) and a polygenic risk score (PRS) on cardiovascular risk factor modification.

**Objectives:**

VOLTAIRE evaluates whether integrating CTCA and PRS into risk counseling enhances adherence to lifestyle and pharmacological interventions, ultimately improving cardiovascular outcomes among patients with T2D.

**Methods:**

VOLTAIRE is a prospective three‐arm, parallel‐group, randomized controlled trial enrolling participants aged 40 years or older with T2D and no established atherosclerotic CVD. Participants are randomized 1:1:1 to receive: (1) risk factor counseling plus CTCA result, (2) risk factor counseling plus PRS result, or (3) standard risk factor counseling (control). Nurse‐led motivational interviewing is used for risk counseling. The primary outcome is change in non‐calcified plaque volume measured by serial CTCA at 12 months. Secondary outcomes include low‐density lipoprotein cholesterol levels, adherence to medication, patient engagement, CVD knowledge improvements, and psychological outcomes over 12 months. Enrollment began in August 2023.

**Discussion:**

VOLTAIRE seeks to determine if coupling nurse‐led risk factor counseling with personalized CTCA or PRS information improves cardiovascular outcomes, adherence, and participant engagement in T2D management.

AbbreviationsCACcoronary artery calciumCADcoronary artery diseaseCTCAcomputed tomography coronary angiographyCVDcardiovascular diseasePRSpolygenic risk scoreT2Dtype 2 diabetesVOLTAIREEValuation Of poLygenic scores and CT imAging In Risk factor modification in patients with diabetes

## Introduction

1

Cardiovascular disease (CVD) remains a leading cause of morbidity and mortality globally, imposing a significant burden on healthcare systems and economies [1, 2]. The situation is even more complex in patients with type 2 diabetes (T2D), which is an independent risk factor for all forms of CVD [3]. Individuals with T2D are up to 3 times more likely to experience a cardiovascular event compared to those without diabetes, associated with a significant reduction in life expectancy of up to 5 years [4, 5].

Given the significant clinical impact of CVD on patients with T2D, integrated management of both conditions has become increasingly important. Multifactorial approaches targeting hyperglycemia, hypertension, and dyslipidaemia, combined with lifestyle changes, are essential for preventing CVD in this high‐risk population [6, 7]. Effective interventions must include medical management alongside education, counseling, and behavioral support to ensure sustained risk factor control [8]. However, optimal implementation of guideline‐based prevention in T2D remains a global challenge [7].

In recent years, addressing these challenges has led to increasing interest in using advanced tools, such as cardiac computed tomography (CT) imaging and polygenic risk scores (PRS), to improve engagement and enhance behavioral modification. Cardiac CT imaging directly visualizes coronary artery atherosclerosis, guiding risk factor modification and potentially motivating patients by showing their own coronary disease [9, 10]. This visual feedback has been associated with improved medication adherence and commitment to recommendations [11, 12, 13].

Genomic advancements have also highlighted the significant genetic predisposition for coronary artery disease (CAD), with heritability estimates at 40%–60% [14]. Genome‐wide association studies have identified numerous single nucleotide variants contributing to cardiometabolic diseases, enabling the development of PRS [15, 16]. PRS offers a comprehensive estimate of genetic risk, supporting personalized interventions and encouraging healthier behaviors, as shown in some studies [16, 17, 18]. Despite the potential of these tools, existing studies and systematic reviews report mixed evidence on the ability of CT imaging and PRS to produce sustained risk factor modification [19, 20, 21, 22]. Their optimal role in routine care remains unclear.

The EValuation Of poLygenic scores and CT imAging In Risk factor modification in patients with diabetes (VOLTAIRE) trial seeks to address this gap by evaluating whether integrating personalized cardiovascular risk information from CT coronary angiography (CTCA) and a PRS into nurse‐led risk factor counseling for patients with T2D can enhance adherence to lifestyle and pharmacological interventions. By incorporating visual feedback from CTCA and personalized PRS reports, this trial aims to empower patients to take an active role in managing their cardiovascular health, potentially leading to meaningful improvements in risk factor modification.

## Methods

2

### Study Design

2.1

The VOLTAIRE trial is a prospective, three‐arm, parallel‐group, randomized controlled trial. Participants are randomized (1:1:1) to: (1) risk factor counseling plus CTCA plaque burden, (2) risk factor counseling plus PRS information, or (3) standard risk factor counseling (control). The study is being conducted at a single site in a metropolitan hospital in Melbourne, Australia, with follow‐up assessments at 6 and 12 months. Recruitment targets individuals with T2D via diabetes outpatient clinics, general practice networks, and community advertisements (flyers, social media) around the hospital and co‐located university campus. This strategy enables a diverse patient sample and supports generalizability. While hospital‐based recruitment may bias toward patients engaged with healthcare, inclusion of community participants and quota sampling for gender balance mitigate this risk. An overview of the trial is presented in Figure 1.

**Figure 1 clc70363-fig-0001:**
[figure not shown]
VOLTAIRE trial design. Participants aged ≥ 40 years with T2D and no established CVD undergo baseline assessment including CTCA and PRS measurement. Individuals with clinically significant coronary disease are enrolled in an observational registry. Eligible participants are randomized 1:1:1 to one of three groups: (1) CTCA results with nurse‐led risk factor counseling, (2) PRS results with counseling, or (3) counseling only. Follow‐up includes medication review, lifestyle and cardiovascular event monitoring, and a 12‐month end‐of‐study CTCA and evaluation. Abbreviations: CTCA, Computed tomography coronary angiography; CVD, Cardiovascular disease; PRS, Polygenic risk score; T2DM, Type 2 diabetes mellitus.

### Participants

2.2

Inclusion criteria were age ≥ 40 years, T2D managed with lifestyle modification or glucose‐lowering medication, and no history of clinically manifest CVD. Participants required acceptable imaging quality as determined by the Victorian Heart Institute Atherosclerosis Imaging Core Lab (VHI‐AICL).

Exclusion criteria included inability to provide written informed consent, unwillingness to undergo serial evaluation, or clinically manifest CVD. Participants with significant coronary disease on baseline CTCA (≥ 50% stenosis in the left main or ≥ 70% in any epicardial artery) were excluded for safety, as masking would not be possible. Individuals unable to complete study procedures, in the investigator's opinion, were also excluded (Table 1).

**Table 1 clc70363-tbl-0001:** VOLTAIRE eligibility criteria.

Inclusion criteria	Exclusion criteria
Age 40 years or older, Established diagnosis of type 2 diabetes, No history of clinically manifest CVD, Having acceptable imaging quality as deemed by the VHI‐AICL	Unable to provide written informed consent Unwilling to be followed for serial evaluation Clinically manifest CVD Clinically significant coronary disease on CT coronary angiogram (≥ 50% in the left main coronary artery or ≥ 70% in any epicardial coronary artery) Unable to participate in the study or complete protocol required assessments in the opinion of the Investigator

Abbreviations: CTCA, computed tomography coronary angiography; CVD, cardiovascular disease; VHI‐AICL, Victorian Heart Institute Atherosclerosis Imaging Core Lab.

Recruitment ran from August 2023 to June 2025, enrolling 147 participants, with 79 randomized: 26 to the CTCA group, 27 to the PRS group, and 26 to the control group.

### Interventions

2.3

#### Conceptual Framework

2.3.1

The conceptual framework for the VOLTAIRE trial is based on Bandura's Self‐Efficacy Theory (Figure 2). Self‐efficacy refers to an individual's belief in their ability to perform behaviors that lead to specific outcomes [23, 24, 25]. This theory posits that higher self‐efficacy enhances motivation, persistence, and resilience, thereby improving behavioral change and

**Figure 2 clc70363-fig-0002:**
[figure not shown]
Conceptual framework–Bandura's self‐efficacy. The framework illustrates how participant characteristics influence healthcare behaviors and expected outcomes through self‐efficacy. Self‐efficacy is supported by five sources: enactive self‐mastery, role modeling, verbal persuasion, emotional and physiological states, and imaginal experiences. Improved self‐efficacy promotes behavioral change and cardiovascular risk reduction. Abbreviation: CVD, Cardiovascular disease.

performance. In the context of cardiovascular risk management, fostering self‐efficacy can empower participants to engage more effectively in lifestyle changes and adhere to recommended treatments, ultimately improving health outcomes.

#### CT Coronary Angiography (CTCA)

2.3.2

Participants undergo CTCA at baseline, with a repeat scan at 12 months for those randomized. CTCA is performed using multi‐detector row scanners (Aquilion One Prism or Insight; Canon Medical Systems Corp., Otawara, Japan). Beta‐blockers and sublingual nitroglycerine are administered prior to achieve a heart rate of <65 beats/min and coronary vasodilation. Iodinated contrast (60–90 mL, 350 mg iodine per mL [Omnipaque; GE Healthcare, Chicago, IL, USA]) is injected at 5 mL/s. Acquisition is automatically triggered at 300 Hounsfield units in the arterial phase using bolus tracking in the descending aorta. Scan parameters include detector collimation 280–320 × 0.5 mm, tube current 100–800 mA (body mass index [BMI]‐dependent), and tube voltage 120 kV (BMI ≥ 25 kg/m^2^) or 100 kV (BMI < 25 kg/m^2^). Images are reconstructed with a 512 × 512 matrix, 0.5 mm slice thickness, sharp convolution kernel, and deep learning‐based reconstruction (Advanced intelligent Clear‐IQ Engine [AiCE], Canon Medical Systems, Otawara, Japan). All CTCA scans are clinically co‐reported by an experienced radiologist and cardiologist according to Society of Cardiovascular Computed Tomography guidelines [26]. If no obstructive CAD (≥70% stenosis in a major epicardial coronary arteriy or ≥50 stenosis in the left main) is detected, results remain blinded until trial completion. Participants with obstructive CAD have reports released, undergo clinical follow‐up, and are enrolled in the observational registry. Incidental non‐cardiac findings are communicated to participants and their general practitioners (GP) for follow‐up.

Participants randomized to receive their CTCA results (Group 1) are given a layperson report co‐designed with Monash Health consumer representatives to ensure clarity and relevance (Figure 3a). The iterative process incorporated consumer feedback to refine content and format. The report summarizes coronary artery stenosis extent in simple terms with visual aids, detailing plaque presence and severity by artery, and categorizing CAD as absent, mild, moderate, or severe. End‐of‐study CT scans use the same equipment and parameters as baseline.

**Figure 3 clc70363-fig-0003:**
[figure not shown]
(a) VOLTAIRE trial CT report. This example report visually summarizes plaque presence and severity, and categorizing blockages as no plaque, 1%–50% blocked, or >50% blocked. Illustrations and actual CT images help participants understand the extent of their coronary artery disease. An overall severity scale contextualizes the results, ranging from no disease to severe blockage. (b) VOLTAIRE trial PRS report. This example report illustrates a participant's PRS for heart disease. The visual places the individual's score within a population distribution ranging from low to high genetic risk. Color coding and simple language help communicate risk levels in an accessible and easily understood format.

#### CTCA Quantitative Plaque Analysis

2.3.3

All image analysis will be performed in the VHI‐AICL by trained analysts using licenced artificial intelligence (AI)‐enabled research software (Autoplaque v3.0, Cedars‐Sinai Medical Center, Los Angeles, CA, USA). Image quality will be assessed prior to analysis, with scans excluded if uninterpretable due to artefacts or missing data. The analyst will define proximal and distal plaque limits, after which adaptive scan‐specific Hounsfield unit (HU) thresholds for plaque components will be auto‐generated. Contouring of the vessel wall and lumen will be automatic, with manual adjustment as required. Plaque is defined as all voxels located between the vessel and luminal boundaries. Per‐lesion volumes (mm^3^) will be calculated for total, calcified, non‐calcified, and low‐attenuation plaque (<30HU). The respective plaque burdens (%) will be calculated as: plaque volume ÷ analyzed vessel volume × 100. Plaque volume and burden measurements for the entire coronary tree will be summed on a per‐patient level. Per‐lesion plaque measurements across the coronary tree will be summed at the per‐patient level.

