### Outcomes

2.4

The primary objective is to assess the impact of personalized cardiovascular risk information, derived from CTCA and PRS, on cardiovascular risk factor modification in individuals with T2D (Table 3). The primary outcome is change in non‐calcified plaque volume on CTCA at 12 months. Non‐calcified plaque volume was selected because it reflects a more biologically active component of coronary atherosclerosis and may be more responsive to risk factor modification over relatively short timeframes.

**Table 3 clc70363-tbl-0003:** VOLTAIRE trial objectives and outcomes.

Primary outcome
– Change in non‐calcified plaque volume
Secondary outcomes
– Achievement of an LDL‐C < 1.8 mmol/L – Intensification of lipid‐lowering therapy, defined as any of the following—increase in the intensity of statin prescribed, addition of ezetimibe, PCSK‐9i – Prescription of a guideline‐recommended statin – Reporting of high levels of adherence to their lipid‐lowering therapy – Level of patient activation and engagement in their care during the study period, compared with baseline – Mental health responses (psychological and emotional reactions) after receiving PRS or CTCA results, including personal perceived risk, personal perceived health‐related quality of life, anxiety, depression or other mental health issues – Change in 5‐year CVD risk
Exploratory outcomes
– Incidence of cardiovascular events – Achievement of all three modifiable risk factor goals: LDL‐C < 1.8 mmol/L, systolic blood. pressure ≤ 130 mmHg, and smoking cessation – Change in hsCRP – Change in HbA1c – Changes in additional imaging parameters, including total atheroma volume, calcified plaque volume, percent atheroma volume, PCAT and epicardial fat volume and density – Achievement of an LDL‐C < 1.8 mmol/L at any time during follow up
Implementation outcome
– Appropriateness, feasibility, and acceptability of the CTCA or the PRS intervention from participants' perspectives

Abbreviations: AE, adverse event; CTCA, computed tomography coronary angiography; CVD, cardiovascular disease; HbA1c, glycated hemoglobin A1c; hsCRP, high‐sensitivity C‐reactive protein; LDL‐C, low‐density lipoprotein cholesterol; PCAT, pericoronary adipose tissue; PCSK‐9i, proprotein convertase subtilisin/kexin type 9 inhibitors; PRS, polygenic risk score.

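### Plaque burden is a percentage, yet the article sums it per patient without stating the common denominator that would make the sum valid; burden-type imaging measures are affected, the primary outcome is not

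*Protocol article*

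**What the plan says.** All the relevant text on measurement is in section 2.3.3 (CTCA Quantitative Plaque Analysis) of the protocol article. In order:

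- The region measured is set lesion by lesion: "The analyst will define proximal and distal plaque limits".
- Per-lesion "volumes (mm^3^) will be calculated for total, calcified, non‐calcified, and low‐attenuation plaque (<30HU").
- Burden is then a ratio: "The respective plaque burdens (%) will be calculated as: plaque volume ÷ analyzed vessel volume × 100".
- Aggregation is by addition, for volume and burden alike: "Plaque volume and burden measurements for the entire coronary tree will be summed" per patient.
- The closing sentence repeats the rule and names the level being added: per-lesion "plaque measurements across the coronary tree will be summed at the per‐patient level".

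The section does not say whether the vessel volume in the denominator belongs to the lesion, the artery or the whole analysed tree. It gives no pooled ratio or weighted mean for burden.

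In section 2.4 and Table 3 the primary outcome is change in non-calcified plaque volume. The only listed outcome that resembles a burden is exploratory, in the imaging group that includes "percent atheroma volume, PCAT and epicardial fat volume and density".

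**The concern.** One rule is applied to two kinds of quantity. A volume is additive: the patient's total is the sum over lesions, however the lesions are divided. A percentage is not, unless all the percentages share a denominator.

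The word linking the burdens to the volumes just listed, and the analyst-set limits, both point to a denominator specific to each lesion. On that reading the patient-level figure is no longer a proportion of anything. It grows with the number of lesions, and it changes if one stretch of plaque is marked as two. Since the trial studies change over 12 months, a difference in how lesions are delineated at the two scans would enter the change score as if it were disease.

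At stake is whether a burden measure reported from this trial could be interpreted. No primary or secondary outcome depends on it.

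**Working it through.** **The plan's own figure.** The article gives no number for burden. Its one relevant calculation, in section 2.7.1, concerns volume: 30 per group, 80% power, difference 8 mm³, SD 11 mm³, alpha 0.83%, and one-third of the variability explained by baseline. The adjusted SD is 11 × √(1 − 1/3) = 8.98 mm³. A two-sided comparison of two means by the normal approximation then needs 31 per group, and 30 per group gives 79.1% power. That agrees closely with the stated figure. Burden does not enter it, so nothing below changes it.

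**The two candidate definitions.** Let lesion *i* have plaque volume pᵢ and analysed vessel volume vᵢ.

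- Sum of burdens, as written: S = Σ (100 × pᵢ / vᵢ)
- Pooled burden: B = 100 × Σpᵢ / Σvᵢ

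B is the average of the lesion burdens weighted by vᵢ, so it cannot exceed the largest of them. S is the number of lesions times their simple average, so it has no ceiling at 100%.

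The documents give no lesion volumes. Those below are assumed, for illustration.

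**Check 1: splitting a lesion.**
- One lesion of 100/250 mm³: S = B = 40%.
- Same tissue marked as two lesions of 50/125 mm³: S = 40 + 40 = 80%; B = 100 × 100/250 = 40%.

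**Check 2: three lesions of 40/100, 24/80 and 30/60 mm³.**
- S = 40 + 30 + 50 = 120%.
- B = 100 × (40 + 24 + 30) / (100 + 80 + 60) = 100 × 94/240 = 39.2%.

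**Check 3: dependence on lesion count.** For *k* lesions of 45% each, S = 45, 90, 135 and 180% for k = 1, 2, 3 and 4. B stays at 45%.

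**Check 4: what the denominator would have to be.** Take plaque volumes of 100, 80 and 60 mm³ in three arteries with vessel volumes of 900, 600 and 700 mm³ (total 2200 mm³).

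| Denominator | Terms (%) | Sum (%) | Pooled (%) |
|---|---|---|---|
| Each artery's own volume | 11.1, 13.3, 8.6 | 33.0 | 10.9 |
| One whole-tree volume, 2200 mm³ | 4.55, 3.64, 2.73 | 10.9 | 10.9 |

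The sum is therefore right under a single whole-tree denominator. It fails under lesion-level denominators (checks 1 to 3) and artery-level denominators.

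**The case against.** The strongest defence is that the denominator is undefined rather than wrong. The article speaks of vessel volume, not lesion or segment volume, and the next sentence refers to the whole coronary tree. If one tree-wide volume is meant, per-lesion burdens add exactly to the patient's burden (check 4). The link between burdens and volumes could also refer to the plaque components rather than to lesions. Further, the last two sentences of the section nearly repeat each other, which suggests loose drafting, and the article condenses a fuller plan that is not shown.

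This stands in part. It rules out saying flatly that the trial will compute an invalid measure. It does not remove the point, because the article itself states a formula and an aggregation rule, and the two fit together only under a denominator that it does not state. The surrounding wording is per-lesion.

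Three stronger readings might be inferred, and the documents do not support them.

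- **That the rule would show progression while true burden falls.** One can build a case in which the three lesions of check 2 each shrink by 10% and a new 10/40 mm³ lesion appears. The pooled ratio over marked lesions then drops from 39.2% to 33.8%, but only because 40 mm³ of vessel joins the denominator. Plaque goes from 94 to 36 + 21.6 + 27 + 10 = 94.6 mm³. Over the same segments at both scans, assuming no earlier plaque in the new one, burden goes from 94/280 = 33.6% to 94.6/280 = 33.8%. It is essentially flat.
- **That percent atheroma volume is this burden.** Table 3 lists it without a formula, and section 2.3.3 does not name it. The link is likely, since burden is the only percentage plaque measure defined there, but it is an inference.
- **That the main result is at risk.** The primary outcome is a volume, and volumes are correctly summed.

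**Conclusion.** The point holds as a defect of wording with a real consequence for burden-type measures. As stated, the per-patient burden is valid only under a common whole-tree denominator that section 2.3.3 does not give. On the more natural per-lesion reading, it depends on lesion count and can exceed 100%: 80% instead of 40% for a split lesion, and 120% instead of 39.2% for three lesions. Those sizes rest on assumed volumes; the dependence on lesion count does not.

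The reach is small. At most it touches burden measures and, probably, one exploratory outcome. Section 2.5 says that outcome assessors are blinded, so the expected harm is a noisy measure that is hard to interpret rather than an evident bias between arms. The primary outcome, the secondary outcomes and the sample size are untouched. Severity is minor and confidence moderate, because the denominator is not defined.

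**What to change.** In section 2.3.3, and in the imaging charter and analysis plan if they carry the same sentence, restrict summation to volumes and define the patient-level burden separately:

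*Plaque volumes will be summed over lesions for each patient. Patient-level burden will be 100 × (sum of plaque volumes) ÷ (sum of analysed vessel volumes), over the same coronary segments at baseline and 12 months.*

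If a whole-tree denominator was intended all along, say so; the result is then the same ratio. State also whether percent atheroma volume in Table 3 is this quantity for total plaque.

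The same-segments condition matters because a ratio taken only over marked lesions still shifts when a lesion is marked at one scan and not at the other.

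The cost is about one sentence. The plaque volumes are planned outputs, and the burden formula already requires vessel volumes. No new scan is needed. Where a segment has a lesion at only one scan, its vessel volume must also be read at the other. The article describes the image analysis in the future tense, so this can be settled before the measurements are made. The primary analysis does not change.
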